### Safety endpoints

Subjects are monitored throughout the study for possible development of AE. All AEs are recorded on the specific form in the Case Report Form (CRF). Any changes in relevant laboratory parameters are also assessed. For all AEs, a relative risk (RR) and also the frequency, severity and seriousness will be measured.

### Design and sample size calculation

The study is an unblinded, randomised controlled trial, enrolling asymptomatic school children, either gender. At baseline, month four, and month eight, IPT with SP or SP-PQ is given. SP is administered as a single treatment dose. However, PQ is given as two doses with a 24-hour interval. IPT is administered at four month intervals in line with the long half-lives of the drugs and for compliance. Each treatment arm will be compared to the control group of untreated participants. Due to the prevalence of STH and schistosomiasis in the study area all participants are treated with albendazole or praziquantel according to the WHO guidelines [26]. Before the study, parents or guardians and children were informed about the objectives and the design of the study during organised meetings at schools.

Within each school, each schoolchild is randomly assigned to one of the two intervention groups or the control group as follows: IPT-SP, IPT-SP-PQ and no-treatment. Each study arm consists of one-third of all individuals.

To estimate the statistical power of our studies, we used an effect size of 0.56 g/dl mean Hb level improvement by the antimalarial IPT compared to the control treatment. This effect size was based upon a previous study.

A previous study estimated the mean Hb concentration of 13.01 g/dl respectively in schoolchildren with IPT and 12.45 g/dl without [27]. The sample size of the study is all schoolchildren of two schools selected within the nearest schools to the regional hospital centre. The overall number of schoolchildren in the two schools is estimated to be 1,300 (650 in each school). By excluding 200 children of the sixth primary school year (100 per school), and accounting for 20% cancelation and 30% to 40% absenteeism, a realistic sample size of 616 individuals is reached for the complete IPT treatment schedule. Using this effect size and sample size, power estimates were performed by Monte Carlo simulation. In each run, a dataset was simulated assuming the within-subject variance and between-subject variability was 16, and putting in effect size to 1. The power was then estimated by fitting a linear mixed model to the data (Hb level versus treatment, time and time:treatment interaction) and testing the significance of the interaction term. The power is then equal to the fraction of times the interaction term was significant, using a significance level of 5%. A sample size of 616 offers 100% power to detect superiority between the control and the intervention groups. For the non-inferiority of SP versus SP-PQ, this sample size has over 91% power to detect a difference in effect less than 0.27 g/dl (<50%).

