### Study procedures

#### *Baseline, enrolment and treatment allocation*

General information on each school regarding composition, water sources, sanitation, health services, and current and previous treatments are collected by questionnaire. The social, economic and demographic patterns are recorded, physical/clinical and complementary examinations are performed, and study treatments and possible co-medications are given according to the study treatment allocation and the participant’s health status (see Table 1).

**Table 1 T1:** Follow-up chart of study participants

**Timeline in months**	**Baseline**	**4**	**8**	**12**
Informed consent	X			
Socio-economic and demographic	X			X
History (symptoms)	X	X	X	X
Examination (clinical)	X			X
Temperature	X	X	X	X
School achievement	X			X
Blood film	X	X	X	X
Hemoglobin (hemocontrol)	X	X	X	X
Thin and thick smear	X	X	X	X
Plasma sample	X			X
Filter paper PCR	X			X
Stool and urine sample	X			X
Malaria treatment^b^	X	X	X	X
Anthelminthic treatment	X	X^a^	X^a^	X
Adverse events	X	X	X	X
Concomitant medications	X	X	X	X

^a^only albendazole is given to participants. ^b^all participants will receive SP at Month 12 irrespective of the treatment allocation. In lines: we have the timelines (in months) that are displayed as baseline, month 4, month 8 and month 12. In columns are the study tasks that are performed and the parameters that are collected. X means perform this task. Blank cells mean that the specific activity will not be performed at the corresponding timeline.

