## Study drugs

### Investigational products

#### *Sulfadoxine–Pyrimethamine (SP)*

Sulfadoxine–Pyrimethamine is an established drug used for uncomplicated malaria in children and adults and for IPT in pregnant women. The safety and efficacy of SP has been widely established in infants and children in clinical trials. For the current study the Fansidar brand of SP is used. Fansidar is supplied as scored tablets, containing 500 mg sulfadoxine and 25 mg pyrimethamine unit doses. Sulfadoxine and pyrimethamine are folic acid antagonists. Sulfadoxine inhibits the activity of dihydropteroate synthase whereas pyrimethamine inhibits dihydrofolate reductase. *In vitro*, sulfadoxine and pyrimethamine are active against the asexual erythrocytic stages of *P. falciparum*. SP may also be effective against strains of *P. falciparum* resistant to chloroquine. Fansidar is approved and commercialised for the treatment of uncomplicated malaria and the prevention of malaria.

Owing to its slow elimination profile, levels of SP sufficient to inhibit parasite growth persist for 60 days after treatment, providing a period of post-treatment prophylaxis during which successful development of a blood-stage infection is prevented. After administration of one tablet, peak plasma levels for pyrimethamine (approximately 0.2 mg/L) and for sulfadoxine (approximately 60 mg/L) are reached after about four hours. The volume of distribution for sulfadoxine and pyrimethamine is 0.14 L/kg and 2.3 L/kg, respectively. Plasma protein binding is about 90% for both pyrimethamine and sulfadoxine. A relatively long elimination half-life is characteristic of both components. The mean values for plasma elimination half-lives are up to 11 days for sulfadoxine and 5 days for pyrimethamine, mainly via the kidneys [28].

Fansidar is given as a single oral dose of ½ tablet of 500 mg sulfadoxine - 25 mg pyrimethamine per 10 kg of weigh: 1 tablet for weight less than 20 kg, 1.5 tablets for 20 to 29 kg, and 2 tablets for children who weigh 30 kg or more.

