### Treatment administration

The study treatment is administered under the direct supervision of a study nurse. Study drugs are given to the children consistent with the investigational brochure of each product. After drug administration, children will be kept for thirty minutes in the class. In case vomiting occurs within 30 minutes of administration a dose is repeated in full. This event is documented in the CRF. If vomiting persists beyond two additional doses, the child is withdrawn from the study.

Upon arrival at a school, an inventory is performed and a drug receipt log filled out and signed by the staff. Accountability for the drug at all school sites is the responsibility of the principal investigator. The investigators ensure that the drug is used only in accordance with this protocol. Accountability records include dates, quantities, lot numbers, expiration dates, and patient numbers.

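### The second piperaquine dose gives the SP-PQ arm alone a staff contact at 24 hours, so AE relative risks against SP-PQ mix drug effect with ascertainment

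*Protocol article*

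**What the plan says.** Design and sample size calculation sets the dosing: "SP is administered as a single treatment dose. However, PQ is given as two doses with a 24-hour interval". It also sets the rounds: "At baseline, month four, and month eight, IPT with SP or SP-PQ is given". The same section describes the trial as unblinded, with a control group given no IPT.

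Treatment administration says "The study treatment is administered under the direct supervision of a study nurse" and "After drug administration, children will be kept for thirty minutes in the class". The section on sulfadoxine–pyrimethamine says that peak plasma levels "are reached after about four hours".

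Table 1 (Follow-up chart) marks the adverse-events row at all its time points, for every arm alike. Its legend reads: "In lines: we have the timelines (in months) that are displayed as baseline, month 4, month 8 and month 12". There is no day-after column.

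Safety endpoints calls for monitoring throughout the study and recording of every AE, and fixes the measure: "For all AEs, a relative risk (RR) and also the frequency, severity and seriousness will be measured". It names neither a time window nor a route of detection. Comparing the safety of SP with SP-PQ is secondary objective 2.

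Between visits, all arms share the same routes: teachers phone the site investigator about absence or sickness, parents are told to bring an unwell child to the health centre, and health-centre records go on the CRF.

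**The concern.** A relative risk for AEs compares treatments fairly only if events have the same chance of being noticed in each arm. Here one arm has a staff contact that the others lack, and it falls on the day after dosing, when transient reactions are most likely to be seen or mentioned. The 30-minute wait after the first dose does not make up for this in the SP arm, because by the article's own figure it ends well before the SP peak at about four hours. After it, the next scheduled AE assessment for an SP child is about four months away.

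At stake is secondary objective 2. SP-PQ could show an excess of mild events over SP, and over control, that comes partly from being seen once more per round. Open allocation adds to this, since child, parent and nurse all know who received the extra drug.

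**Working it through.** The article gives no AE rate and no safety sample size, so there is no figure of its own to reproduce. The check has two parts.

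**1. Contacts per arm, from the article**

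| | SP-PQ | SP | Control |
|---|---|---|---|
| Scheduled visits with AE recording (baseline, months 4, 8, 12) | 4 | 4 | 4 |
| Second-dose contacts at 24 hours (one per round, 3 rounds) | 3 | 0 | 0 |
| Total scheduled staff contacts | 7 | 4 | 4 |
| Supervised IPT dosing occasions | 2 × 3 = 6 | 1 × 3 = 3 | 0 |

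The scheduled AE visits are balanced. The imbalance is the three second-dose contacts. Because every AE is to be recorded, an event noticed or volunteered there would go on the CRF.

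**2. How large the distortion could be (illustration)**

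Let the true AE risk p be equal in SP and SP-PQ. All of the following are assumptions:
- s: share of AEs captured by routes common to all arms (scheduled visits, teachers, health centre)
- f: share of AEs present at the 24-hour contact
- 0.9: chance that an AE present at that contact is recorded there

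Captured share in SP = s.
Captured share in SP-PQ = f × [1 − (1 − s)(1 − 0.9)] + (1 − f) × s.
Apparent RR = captured share in SP-PQ ÷ s.

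- Low case, f = 0.1, s = 0.9: (0.1 × 0.99 + 0.9 × 0.9)/0.9 = 0.909/0.9 = 1.01
- Middle case, f = 0.3, s = 0.6: (0.3 × 0.96 + 0.7 × 0.6)/0.6 = 0.708/0.6 = 1.18
- High case, f = 0.6, s = 0.3: (0.6 × 0.93 + 0.4 × 0.3)/0.3 = 0.678/0.3 = 2.26

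For f from 0.1 to 0.6:

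| Common-route capture s | Spurious RR |
|---|---|
| 0.9 | 1.01 to 1.06 |
| 0.6 | 1.06 to 1.36 |
| 0.3 | 1.21 to 2.26 |

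The article's sample size of 616 gives 616/3, about 205 per arm. With p = 0.3 (assumed), the recorded proportions are 0.3 × 0.708 = 21.2% against 0.3 × 0.6 = 18.0% in the middle case, and 0.3 × 0.678 = 20.3% against 0.3 × 0.3 = 9.0% in the high case. By the normal approximation at two-sided 5%, the chance of a nominally significant excess in SP-PQ is about 13% and about 90% respectively. It would be 2.5% in that direction with no bias.

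If contact times are the same in all arms, the extra term disappears and the ascertainment part of the RR is 1.00.

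**The case against.** Several counter-arguments are sound and limit the point.

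- **No AE assessment is written in at 24 hours for SP-PQ either.** Table 1 treats all arms alike, and its legend, "Blank cells mean that the specific activity will not be performed at the corresponding timeline", settles nothing because there is no 24-hour column to leave blank. The imbalance is inferred from the supervised second dose together with the rule that all AEs are recorded. A reader should not conclude that SP-PQ children are formally questioned more often.
- **The passive routes are common to all arms.** Randomisation is individual within school, so the same teachers watch all three groups. If these routes capture nearly everything, the bias is negligible (RR 1.01 to 1.06). However, they depend on a child being absent, sick or unwell. Safety assessment defines a mild AE as one that is easily tolerated, and such events would seldom prompt a phone call or a health-centre visit.
- **The second PQ dose is real added exposure.** Reactions to it are drug effects and belong in the comparison. A reader might infer that the relative risks measure ascertainment instead of the drugs. The article does not support that: they would mix the two.
- **SP versus control.** A reader might infer that both active arms will look worse than control. SP has no 24-hour contact, so that comparison is untouched by it. Controls lack the observation after an IPT dose, but they attend the same visits and also receive anthelminthics.
- **Several-fold relative risks.** These arise only if every AE over 12 months were detectable at the 24-hour contact and the common routes captured few of them. The article gives no basis for that.
- **A condensed article may leave AE procedures to the full protocol or SAP.** That is fair for detail. The point rests on what is stated: the dosing asymmetry, the visit schedule, and a relative risk for all AEs.

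**Conclusion.** The point holds in limited form. Followed as written, the plan gives SP-PQ three extra staff contacts, each 24 hours after a first dose, with no matching contact in SP or control, while all AEs feed a relative risk. The SP-PQ versus SP and SP-PQ versus control comparisons are open to bias in a known direction, against SP-PQ, mainly for early mild events.

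The size cannot be determined from the article. The range of 1.01 to 2.26, with 1.18 in the middle, rests entirely on assumed values of f, s and the 0.9 capture rate, on equal true risk, and on AEs actually being recorded at the second-dose contact. It shows that the effect could be trivial or material. It is not an estimate. The change is worth making because it is cheap and removes the 24-hour imbalance at source.

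**What to change.** On the day after each course (baseline, months 4 and 8), put the same short AE checklist to children in all three arms. Staff are already at the school that day for the second PQ dose. In the SP-PQ arm, ask it before that dose, so that the answers cover the same 24 hours everywhere. The article gives the trial as recruiting, so the checklist can start at the next round in all arms together, with rounds already completed handled by the fallback.

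Fallback, if the checklist is not adopted: record on the CRF how each AE was detected, and report relative risks by ascertainment route. Show a comparison based only on contacts common to all arms (scheduled visits, teacher reports, health-centre attendance) alongside the all-AE relative risk. Both are needed, because the common-contact version leaves out genuine reactions noticed only at the second dose.

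The checklist costs a few minutes per child and one CRF line per round, and more mild AEs will be recorded in SP and control. The fallback costs a CRF field and analysis wording. Neither alters treatment, and neither removes reporting differences that come from open allocation.

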## Discussion

Little research has been performed on IPTsc in malaria stable transmission. Rohner *et al.*[35] found no effect for IPT with SP monotherapy given at baseline and three months later to schoolchildren. On the other hand, Clarke *et al*. [27] found a reduced prevalence of anaemia by 50% for a 'sulfadoxine-pyrimethamine plus amodiaquine’ IPT combination therapy given three times at four-month intervals at one year follow-up compared to a placebo. They also reported a significant improvement from the IPT intervention on the behavioural and educational achievements of the schoolchildren. Similarly, Nankabirwa *et al*. [36] reported a decreased risk of malaria parasitaemia following 42 days follow-up for dihydroartemisinin-piperaquine (11.7% (95%CI:7.9 to 17.1)) and 'amodiaquine plus SP’ (44.3% (95%CI:37.6 to 51.5)) compared to a SP monotherapy (79.7%(95% CI:73.6 to 85.2)), and to a placebo (84.6%(95% CI: 79.1 to 89.3)).

Our clinical trial is unique in investigating the impact of antimalaria IPT in schoolchildren of hyper endemic areas for longer follow-up, resistance markers for SP at baseline and after 12 months (including break through parasitaemias). Our study is also unique in using piperaquine in combination with SP. Artemisinin derivative has been excluded as it is part of the treatment policies in virtually all malaria endemic countries [37].

The findings of the clinical trial are, therefore, expected to make a major contribution to the public health of youngsters who fail to thrive and grow due to multiple morbidities.

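### The power statement contradicts itself: it adopts an effect of 0.56 g/dl but simulates with effect 1 and variance 16, no units given, so the 100% and over-91% figures cannot be relied on

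*Protocol article*

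**What the plan says.** All of this is in the protocol article, section Design and sample size calculation, unless another section is named.

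- **Effect adopted:** "we used an effect size of 0.56 g/dl mean Hb level improvement by the antimalarial IPT compared to the control treatment". It comes from a previous study with a "mean Hb concentration of 13.01 g/dl respectively in schoolchildren with IPT and 12.45 g/dl without", and 13.01 - 12.45 = 0.56.
- **Effect said to be simulated:** "Using this effect size and sample size, power estimates were performed by Monte Carlo simulation".
- **Inputs then reported:** "a dataset was simulated assuming the within-subject variance and between-subject variability was 16, and putting in effect size to 1". Neither number has a unit, and the effect has no time scale.
- **Test:** the time-by-treatment interaction in a linear mixed model, at 5%, sidedness not stated.
- **Results:** "A sample size of 616 offers 100% power to detect superiority between the control and the intervention groups". For non-inferiority of SP versus SP-PQ, power is put at over 91% for 0.27 g/dl, described as under 50% of the effect.
- **Sample size:** from 1,300 children less 200 in the sixth year, "accounting for 20% cancelation and 30% to 40% absenteeism, a realistic sample size of 616 individuals is reached".
- **Allocation:** one-third per arm (also 1:1:1 under Randomisation and treatment allocation).
- **Hb visits:** baseline and months 4, 8 and 12 (Table 1).

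**The concern.** Two statements about the same simulation disagree. One says it used 0.56 g/dl; the next gives the effect as 1. The variance of 16 is an SD of 4, which is large beside an effect of 0.56 or 1 if they share a unit, and hard to square with near-certain power at about 205 per arm.

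The sample is fixed by the enrolment of two schools, so this paragraph is the only quantitative statement of what the trial can show. A reader told that non-inferiority has over 91% power would take a failed non-inferiority test as informative, when it might only reflect low precision. The sample size has a smaller problem of the same kind: a range is given for absenteeism, but a single figure is carried forward.

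**Working it through.** **Sample size.** 1,300 - 200 = 1,100. 1,100 x 0.8 x 0.7 = 616, the stated figure exactly, using 30% absenteeism. At 40%: 1,100 x 0.8 x 0.6 = 528. One-third of 616 is 205.3 per arm; one-third of 528 is 176.

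**Method.** Random-intercept model with Hb at t = 0, 1/3, 2/3 and 1 year. Sxx = Σ(t - mean)² = 5/9. The between-subject intercept variance cancels. With within-subject variance s²:

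- SE of the 12-month difference = √[(s²/Sxx)(1/n1 + 1/n2)]
- superiority power = Φ(δ/SE - 1.96), two-sided 5%, plus a small opposite-tail term
- non-inferiority power, true difference 0 = Φ(0.27/SE - z), with z = 1.96 (one-sided 2.5%) or 1.645 (one-sided 5%)

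No random-slope variance is added, which favours the plan.

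**Reading A: 16 in (g/dl)², effect is the 12-month difference, N = 616.**
- One arm versus control: SE = √[(16/0.5556)(2/205.3)] = 0.530. Both IPT arms pooled versus control: SE = 0.459.
- Effect 0.56: 18% per arm, 23% pooled.
- Effect 1: 47% per arm, 59% pooled.
- Non-inferiority: Φ(0.27/0.530 - 1.96) = 7%; with 1.645, 13%.
- Monte Carlo runs agreed to within one or two percentage points.
- At N = 528: 16% per arm for 0.56, and 7-12% for non-inferiority.

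**Reading B: effect 1 per visit interval (time coded 0, 1, 2, 3; Sxx = 5), variance 16.**
- SE per interval = √[(16/5)(2/205.3)] = 0.177, so superiority power is 100%.
- The implied month-12 difference is 3 x 1 = 3 units, against a justified 0.56.
- Non-inferiority at 0.27 on this scale: 33% (one-sided 2.5%) to 45% (one-sided 5%).
- Margin rescaled to a unit effect, 0.27/0.56 = 0.48: 78% to 86%.
- With 308 per group the rescaled version gives 100% and 91.7%, close to both stated figures. But 308 is half of 616, and the plan allocates one-third.

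**Reading C: 16 in (g/L)², that is 0.16 (g/dl)², with effect 0.56 g/dl over 12 months.**
- SE = 0.053. Superiority is 100% and non-inferiority is over 99%.
- If the effect of 1 were also in g/L, the ratio to the SD would be that of Reading A and superiority would again be 47-59%. So this reading works only if the reported effect of 1 is set aside or put in a different unit from the variance.

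**What the trial might deliver.** The documents give no Hb variance in g/dl. Assume a residual variance of 0.5 to 1.6 (g/dl)², 205 per arm:

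| Residual variance | SE | Superiority, 0.56 per arm | Non-inferiority, one-sided 2.5% | Non-inferiority, one-sided 5% |
|---|---|---|---|---|
| 0.5 | 0.094 | 100% | 82% | 89% |
| 1.6 | 0.168 | 92% | 36% | 49% |

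At N = 528, non-inferiority (one-sided 2.5%) is 76% and 32%. To reach 91% at N = 616 the residual variance must be about 0.38 (one-sided 2.5%) to 0.47 (one-sided 5%), some 34 to 42 times below 16.

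**The case against.** The strongest reply is that an article condenses its simulation and that what is missing here is a unit and a time scale. A within-child SD of 4 g/dl around a mean of 12 to 13 g/dl is implausible, so the 18% and 7% figures probably describe a unit or scaling slip, not this trial. Effect 1 per visit interval does give 100%. Expressing the margin as a percentage of the effect fits a simulation normalised to 1. Reading 16 as (g/L)² gives over 99% for non-inferiority, which does not contradict a claim of over 91%; adding a child-level slope variance of 0.16 to 0.40 (an assumption) would bring it to about 98% down to 91%.

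Most of this stands. It would be wrong to say that no reading of the inputs yields the stated powers. But each reading that does so needs a step that is unstated or conflicts with the text: a 3-unit difference at month 12, half the sample per arm, or a variance in a unit that is not the effect's. None removes the contradiction between 0.56 and 1.

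Three further inferences are tempting and not supported:

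- **That the simulation omitted the random slope.** The Statistical analysis plan section includes one, but the phrase about between-subject variability does not say intercept only.
- **That 0.56 g/dl is wrong for SP alone**, because the Discussion shows it came from SP plus amodiaquine and cites a trial that "found no effect for IPT with SP monotherapy given at baseline and three months later to schoolchildren". That is a judgement about assumptions; the cited trial gave two courses, this one gives three.
- **That 528 seriously damages the trial.** The 616 refers to completers of the full schedule, absent children are seen on another day, and the mixed model uses incomplete follow-up. The loss of power is modest.

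**Conclusion.** The concern holds in a limited form. The power paragraph contradicts itself on the effect simulated and gives no units or time scale for its inputs. Under the most direct reading, its figures are far from reproducible. The 100% and over-91% claims cannot be relied on as written.

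A reader might conclude from the 18-23% that superiority is underpowered. The documents do not show that: those figures follow from a variance that may carry the wrong unit, and under the assumed variances per-arm superiority at 0.56 g/dl remains about 92-100%. The doubtful figure is the 91% for SP versus SP-PQ, which is not reached anywhere in that assumed range under either one-sided level. The practical harm therefore falls mainly on the SP versus SP-PQ comparison, a secondary objective. The selective use of 30% absenteeism is a real but secondary defect.

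**What to change.** Reconcile the effect of 1 with 0.56 g/dl, stating what each number means. Then re-run the simulation with:

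- 0.56 g/dl as the difference in change over 12 months;
- within- and between-subject variances in stated units, with their source;
- one-third of the children per arm, and the sidedness of each test;
- the mixed model given in the Statistical analysis plan section, including its random slope;
- N = 616 and N = 528;
- non-inferiority assessed as a confidence limit against 0.27 g/dl.

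Restate both powers and say plainly if non-inferiority falls below 91%.

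The cost is a few hours of simulation and one corrected paragraph. No extra children and no design change are needed. The downside is that the stated non-inferiority power will probably be less favourable.
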